#### Alternative activity in times of corona

ECEC teachers prepare fruit and vegetables together with the children at preschool. They will tell parents that they performed this activity at preschool. In addition, they will give parents the information card with practical tips about eating vegetables and helping in the kitchen and the plastic knife to take home. On the back of the information card children can put a sticker when they taste a vegetable at home. Parents will be asked to let their child help in the kitchen at home in the upcoming week.

### **Activity 3 - healthy eating**

Parents and children play a memory game.

Parents will receive a memory game and will be asked to play the game together with their child. When the child finds 2 memory cards that belong together, they can hang the cards

with clothespins to a clothesline in the classroom. Next, ECEC teachers will show an information card with practical tips about healthy eating. Parents will receive a copy of the information card to take home. The back of the information card shows healthy snacks for children. Parents will be asked to let their child choose a healthy snack to try at home in the upcoming week.

Alternative activity in times of corona

Parents will receive the memory game to take home and will be asked to play the game together with their child. In addition, parents will receive the information card with practical tips about healthy eating. The back of the information card shows healthy snacks. Parents will be asked to let their child choose a healthy snack to try at home in the upcoming week.

#### **Activity 4 - portion sizes**

Parents and children decorate a placemat.

Parents will receive a placemat and colours. Children colour the placemat together with parents. Next, ECEC teachers show an information card with practical tips about providing healthy portion sizes.

Parents will receive a copy of the information card and the coloured placemat to take home. Children can help setting the table at home by using the placemat.

Alternative activity in times of corona

Children will colour a placemat at preschool. Parents will receive the coloured placemat and an empty one to take home. Children can colour the placemat together with their parents at home and can help setting the table by using the placemats. In addition, parents will receive the information card with practical tips about providing healthy portion sizes.

#### **Activity 5 - drinking water**

Parents and children decorate a water cup

Parents will receive a water cup and will be asked to decorate the cup together with their child. In the classroom there is a lemonade tap with water (and pieces of fruit). Children can tap water with their decorated cups. Next, ECEC teachers will show an information card with practical tips about drinking water and a poster about the amount of sugar in several sweetened beverages. Parents will receive a copy of the information card. On the back of the information card children can put a sticker when they drink water at home.

Alternative activity in times of corona

Children will decorate a water cup at preschool together with the ECEC teachers. In the classroom there is a lemonade tap with water (and pieces of fruit). Children can tap water with their decorated cups. Parents will receive the decorated cup and the information card with practical tips about drinking water to take home. On the back of the information card children can put a sticker when they drink water at home.

### **Activity 6 - do a physical activity together**

Parents and children carry out a physical activity together.

A physical activity calendar with a parent-child activity for each month of the year will hang in the classroom. Children and parents perform 1 physical activity of the calendar at preschool. This activity is balancing on a line. Balance lines (zigzag, straight and corners) are drawn on to the floor with painter's tape. Children can walk forward, sideways and backwards on the lines with parents. An optional extra challenge is walking on toes or 1 leg. ECEC teachers can add roadblocks/obstacles to step over.

Next, parents will receive a small version of the calendar and an information card with practical tips about exercising together to take home. Parents will be asked to carry out a physical activity at home with their children in the upcoming week. The physical activity calendar will remain hanging in the classroom, so every month there is a different physical activity at home and at the preschool.

Alternative activity in times of corona

Children will do the activity "balancing on a line" together with the ECEC teachers at preschool. ECEC teachers will tell parents that they did this activity at preschool and will give parents the physical activity calendar and information card with practical tips to exercise together to take home. Parents will be asked to do a physical activity from the calendar together with their child at home in the upcoming week.

### **Activity 7 - screen time/playing indoors**

Parents and children do a search game.

Parents will be given a kitchen timer and will be asked to set the timer to 30 seconds or 1 minute. Next, parents will ask their child to search for a certain object or an object with a specific colour. When the alarm goes off, the children stop searching.

Next, ECEC teachers will show an information card with practical tips playing inside and reducing screen time. Parents will receive a copy of the information card to take home and will be told that rules about screen time can be set at home using a timer (for example, a maximum of 5 minutes screen time at a time).

Alternative activity in times of corona

ECEC teachers will perform the search game together with the children at preschools. The teachers will tell parents that they did this activity at preschool and will give parents a short instruction to play the game at home. In addition, parents will receive the information card with practical tips about playing inside and reducing screen time. They will be told that rules about screen time can be set at home using a timer (for example, a maximum of 5 minutes screen time at a time).

### **Activity 8 - exercising together**

Children practice a balance bike trail together with their parents.

ECEC teachers prepare a trail with chalk (a slalom track/objects to stop at) outside. Children practice riding a balance bike on the trail supported by their parents. ECEC teachers give tips for using the balance bike. In addition, there's another trail (climbing on objects/jumping in circles) to do by foot for the children who have to wait for a bike.

A loan system for balance bikes will be set up. Children can take home a balance bike for a week. Parents receive an information card with practical tips for using the balance bike at home.

Alternative activity in times of corona

Children will practice riding a balance bike on the trail at preschool. ECEC teachers will tell parents that they did this activity at preschool. A loan system for balance bikes will be set up. Children can take home a balance bike for a week. Parents receive the information card with practical tips for using the balance bike at home.

### **Activity 9 - playing outside**

Parents and children look outside for a natural treasure.

Parents and children will be shown a poster with an image of a tree. Children and their parents search for a "natural treasure" outside (for example, beautiful leaves). The treasures will then be glued on to the tree, so children and their parents make art from nature.

Next, ECEC teachers will show an information card with practical tips for playing outside. Parents will receive a copy of the information card and will be asked to play outside with their children every day in the upcoming week. In addition, parents receive a list of (free) exercise places in the neighbourhood.

Alternative activity in times of corona

Children and their parents search for a "natural treasure" outside (for example, beautiful leaves). Children bring the treasures to the preschool and glue them on a poster with an image of a tree, so children make art from nature together with the ECEC teachers. Parents will be asked to play outside with their children every day in the upcoming week. In addition, parents receive the list of (free) exercise places in the neighbourhood and the information card with practical tips for playing outside to take home.

### **Activity 10 - sleeping**

Parents and children create a ritual with sleep ritual cards.

Parents will be given sleep ritual cards (with images such as brushing teeth, bedtime story, tucking in). Children and their parents put the cards in a sequence so that it becomes their own sleep ritual. Children can practice 1 of the activities, shown in the sleep ritual cards, on a doll/cuddly toy in the room.

Next, ECEC teachers will show an information card with practical tips about sleeping. Parents will receive a copy of the information card to take home and will be asked to perform the sleep ritual at home in the upcoming week.

Alternative activity in times of corona

ECEC teachers will ask children what things they can do before they go to bed. The teachers will show all sleep ritual card and discuss them with the children. Children can practice 1 of the activities, shown in the sleep ritual cards, on a doll/cuddly toy in the room. ECEC teachers will tell parents that they did this activity at preschool and will give parents 2 A4 to take home, 1 with pictures of 8 sleep ritual cards and 1 with a plain sequence. Children and their parents can cut/tear the sleep ritual cards and glue them in a sequence on the second A4 so that it becomes their own sleep ritual. In addition, parents will receive the information card with practical tips about sleeping to take home and will be asked to perform the sleep ritual at home in the upcoming week.

## 6. METHODS

A detailed description of the study procedures and methods to assess the study parameters can be found in section 6.3. Table 1 shows an overview of the study parameters per study timepoint.

### 6.1 Study parameters/endpoints

#### 6.1.1 Main study parameter/endpoint

Changes in scores on the **ECEC teacher-parent partnership** regarding eating, physical (in)activity and sleeping behaviours in young children. *Assessed by questionnaire at baseline and at 6 months, multiple informed research (teacher informed and parent informed).*

#### 6.1.2 Secondary study parameters/endpoints

##### ECEC TEACHERS

Changes in scores on the **knowledge, attitude and practices** regarding healthy eating, physical (in)activity and sleeping behaviours of young children. *Assessed by questionnaire at baseline and at 6 months.*

Experiences with the toolkit (only applicable for ECEC teachers in the intervention group). *Obtained with a short interview at 6 months.*

##### PARENTS

Changes in scores on the **knowledge, attitude and practices** regarding healthy eating, physical (in)activity and sleeping behaviours of young children. *Assessed by questionnaire at baseline and at 6 months*

Whether or not they performed **parent-child activities at home**. If yes, which activities. If not, why not. *Assessed by questionnaire at 6 months, only applicable for parents in the intervention group.*

Experiences with the toolkit (only applicable for parents in the intervention group). *Obtained with a short interview at 6 months.*

##### CHILDREN

#### **Eating, physical (in)activity and sleeping behaviours**

*Assessed by questionnaire at baseline and at 6 months.*

In times of corona, researchers and parents are not allowed to enter the preschools. Therefore it is not possible to perform the following measurements at preschools. When it is allowed again to enter preschools, the researchers will start performing the measurements and collect data on children's dietary intake, physical activity levels and weight development.

**Dietary intake**

*Parents will be given the option to participate in a 24 hour recall about the dietary intake of their child at baseline and at 6 months.*

**Physical activity**

*Parents will be given the option to participate in a physical activity assessment (accelerometer) of their child at baseline and at 6 months.*

**Height (cm)**

*Measurement at baseline and at 6 months.*

**Weight (kg)**

*Measurement at baseline and at 6 months.*

**Waist circumference (cm)**

*Measurement at baseline and at 6 months.*

**BMI (z-score)**

*BMI ( $\text{kg/m}^2$ ) will be calculated and BMI z-scores will be assessed at baseline and at 6 months.*

**6.1.3 Other study parameters****ECEC TEACHERS**

**Socio-demographic characteristics** (age, sex, ethnicity and educational level).

**PARENTS**

**Socio-demographic characteristics** (age, sex, ethnicity and educational level).

**CHILDREN**

**Socio-demographic characteristics** (age, sex, ethnicity).

**Table 1.** Overview of the study parameters per study timepoint

| TIMEPOINT                                | BASELINE |         |          | 6 MONTHS |         |          |
|------------------------------------------|----------|---------|----------|----------|---------|----------|
|                                          | Teachers | Parents | Children | Teachers | Parents | Children |
| Socio-demographic characteristics | X        | X       | X        |          |         |          |
| Partnership                       | X        | X       |          | X        | X       |          |
| Knowledge                         | X        | X       |          | X        | X       |          |
| Attitude                          | X        | X       |          | X        | X       |          |
| Practices                         | X        | X       |          | X        | X       |          |
| Eating behaviours                 |          |         | X        |          |         | X        |
| Physical (in)activity behaviours  |          |         | X        |          |         | X        |
| Sleeping behaviours               |          |         | X        |          |         | X        |
| Dietary intake                    |          |         | X        |          |         | X        |
| Physical (in)activity             |          |         | X        |          |         | X        |
| Height                            |          |         | X        |          |         | X        |
| Weight                            |          |         | X        |          |         | X        |
| Waist circumference               |          |         | X        |          |         | X        |
| BMI (z-score)                     |          |         | X        |          |         | X        |

## 6.2 Randomisation, blinding and treatment allocation

Randomisation will be performed before the start of the study on the level of preschools within participating childcare organisations. The randomisation will be performed by an independent researcher of the AUAS with the use of computer-generated randomisation lists. It concerns a stratified randomisation by childcare organisation to achieve balance in the number of preschools within each organisation that will receive the intervention or not. As preschools within each organisation differ in location size (and therefore the number of eligible participants), we will 1) order preschools by location size, 2 ) match preschools in pairs based on location size and 3) randomly allocate 1 preschool to the intervention group and the other to the control group. 1 member of the research staff ([name]) will be blinded for allocation and perform final analyses. ECEC teachers, parents and other members of the research staff will not be blinded as the intervention does not allow for this.

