### 6.3 Study procedures

The study period will be 6 months, starting with a baseline measurement and ending with a close-out measurement. All assessments will take place at preschools in Amsterdam, the Netherlands. In times of corona, only questionnaires will be distributed as other measurements at preschools are not allowed.

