
Answering options for the questions are the same as in the questionnaire for ECEC teachers and mean scores per question/scale will be calculated.

The questionnaire for parents also includes questions to obtain data on the eating, physical (in)activity and sleeping behaviours of their child. These questions are based on the 'Sarphati Amsterdam Core set plus questionnaire for 36 months' (24). In addition, some questions are included on the parents' knowledge, attitude and practices about healthy behaviours for young children. These questions are based on the Food and Health Survey 2018 (22), Comprehensive Feeding Questionnaire (25), Preschooler Physical Activity Parenting Practices questionnaire (26), and a questionnaire on maternal efficacy (27). In addition, some questions are compiled by the research staff. Parents can fill in the questionnaire at home (it will take about 30 minutes to fill in the questionnaire). The research staff will visit preschools to collect the questionnaires (1 week after the questionnaires are being provided). To obtain more information about children's dietary intake, parents will be asked to participate in a 24-hour dietary recall at baseline and at 6 months. In times of corona, 24-hour dietary recall sessions will not be performed as parents and researchers are not allowed to enter the preschools. When it is allowed again to enter preschools, the researchers will start to collect data on children's dietary intake. Paper questionnaires will, in times of corona, be distributed (at the door) by ECEC teachers. To obtain input for a process evaluation of the intervention, short interviews with participating parents will be held at 6 months (only applicable for parents in the intervention group). At 6 months, the research staff will ask parents if they would like to participate in a short interview of about 15 minutes and give their opinion about the parent-child activities. If yes, the research staff will note a telephone number and will call the specific parent for the short interview concerning the intervention.

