### 9.2 Recruitment and consent

ECEC teachers will be informed about the research through their supervisor. In addition, the AUAS researchers will visit the locations to provide further information and hand out an information letter and the Informed Consent form. In times of corona, also digital meetings (via Microsoft Teams) will be used to inform ECEC teachers. With a minimum of 1 week time to consider their decision, AUAS researchers will visit (and in times of corona, call) the locations to answer any questions. If ECEC teachers then like to join the research, an Informed Consent in writing is obtained. In times of corona, it is still possible for the researchers to obtain written Informed Consent (the forms can be exchanged at the door). Parents will be informed of the AUAS researchers coming to the location and will be given a short heads up what the research is about by ECEC teachers. AUAS researchers then visit the locations to provide oral information about the research and will hand out written information and the Informed Consent form. Parents will be asked to read the information at home and consider joining the research with their child. The AUAS researchers will revisit the location 1 week after providing the information to answer any questions from the parents and if parents and their children like to join the research, an Informed Consent in writing is obtained. Parents give written permission for themselves and their child to participate. In times of corona, it is not possible to visit the preschools and talk to parents. Therefore, only via ECEC teachers some parents will be recruited. In times of corona, it is still possible for the researchers to obtain written Informed Consent (the forms can be exchanged at the door).

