## **10.3 Annual progress report**

The sponsor/investigator will submit the start date of the trial (date of inclusion of the first participant) to the accredited METC. The sponsor/investigator will submit a summary of the progress of the trial to the accredited METC once a year. Information will be provided on the date of inclusion of the first subject, numbers of subjects included and numbers of subjects that have completed the trial, serious adverse events/ serious adverse reactions, other problems, and amendments.

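### Preschools are randomised before participants are included and measured at baseline, and nothing conceals the allocation from those who recruit; the exposure is greatest for parents recruited through teachers in corona times

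*Protocol*

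**What the plan says.** Protocol section 6.2 sets the timing: "Randomisation will be performed before the start of the study on the level of preschools within participating childcare organisations". Two other sections show what that start is. Section 6.3: "The study period will be 6 months, starting with a baseline measurement and ending with a close-out measurement". Section 10.3 dates the trial from the first inclusion: "start date of the trial (date of inclusion of the first participant".

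Section 6.2 blinds one member of the research staff, who "will be blinded for allocation and perform final analyses". For everyone else it says: "ECEC teachers, parents and other members of the research staff will not be blinded as the intervention does not allow for this".

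Section 9.2 gives two routes for parents. In normal times teachers announce the study, and then "AUAS researchers then visit the locations to provide oral information about the research and will hand out written information and the Informed Consent form"; the researchers come back a week later for questions and consent. In corona times they cannot visit: "Therefore, only via ECEC teachers some parents will be recruited". Section 6.3 (Parents) adds: "Paper questionnaires will, in times of corona, be distributed (at the door) by ECEC teachers".

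For teachers, section 4.1 has all of them approached at each participating preschool. Under section 6.1.1 the primary outcome is the partnership score, reported by both teachers and parents.

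**The concern.** Randomising preschools makes the preschools comparable. It makes the participating individuals comparable only if they enter without the arm influencing who is asked or who agrees. Here the arms exist before the first inclusion, and the people who recruit and respond may know them.

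The corona-time parent route is the most exposed. The teacher is the only channel, is not blinded, and has no instruction on whom to invite and no count to keep. The parent who enters then scores the partnership with the teachers of that preschool. If teachers in one arm tend to reach parents with whom they already work well, the arms differ on the primary outcome before any activity takes place. The baseline score used as a covariate is also collected after allocation.

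The reason given for not blinding is that the intervention makes it impossible. That holds once activities are under way. It does not explain why the arm must be known before consent and baseline. No later analysis can fully repair an imbalance in who entered, so this cannot be left to the SAP.

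**Working it through.** **Order of events.** Section 6.2 puts randomisation before the start of the study. Sections 6.3 and 10.3 start the study with the baseline measurement and the first inclusion. Randomisation therefore precedes both. No section says that the allocation is held back until consent or baseline is complete, and none says when preschools learn it.

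**The plan's own figures (section 4.4).** With two-sided α = 0.05 and 80% power, n per group = 2(1.96 + 0.84)²/d², times the design effect 1 + (m − 1)·ICC, then 15% drop-out.

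- Teachers (d = 0.50, m = 3, ICC = 0.05): 63 × 1.10 = 69.3. Dividing by 0.85 gives 82 and multiplying by 1.15 gives 80. Stated: 80.
- Parents (d = 0.35, m = 6, ICC = 0.02): 129 × 1.10 = 141.9, giving 167 or 164. Stated: 160, which after 15% loss has 78.6% power, or 80% power for d = 0.356.

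The figures reproduce closely enough; the point does not rest on a numerical error.

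**Standard error for parents.** Effective n per arm = 160 × 0.85/1.10 = 123.6. SE = √(2/123.6) = 0.127 SD without baseline adjustment. With a baseline to 6-month correlation r (assumed), SE = 0.127 × √(1 − r²): 0.110 at r = 0.5 and 0.091 at r = 0.7.

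**Size of a recruitment shift (all inputs assumed).** Suppose teachers reach the best fraction p of parents on their own impression, which correlates c with the parent's score at both times. The mean shift is c × k, where k = φ(z_p)/p: 0.80 for p = 50%, 0.64 for 60%, 0.50 for 70%. Baseline adjustment leaves shift × (1 − slope), with the within-arm slope slightly below r because of the selection. Take c = 0.3–0.5 and r = 0.5–0.7, with no true effect.

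| Scenario | Raw difference (SD) | Left after baseline adjustment (SD) |
|---|---|---|
| Intervention best 50–70%, control at random | 0.15–0.40 | 0.05–0.22 |
| Intervention best 50%, control best 70% | 0.09–0.15 | 0.03–0.09 |
| Intervention best 50%, control best 60% | 0.05–0.08 | 0.015–0.045 |
| Same selection in both arms | 0 | 0 |

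The largest residual is 0.40 × (1 − 0.46) = 0.22. The smallest in the first row is 0.15 × (1 − 0.69) = 0.05.

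**Effect on the 5% error rate.** For a residual bias b, rejection = Φ(b/SE − 1.96) + Φ(−b/SE − 1.96). At b = 0.10 SD this is 12.3% with SE 0.127, 14.8% with SE 0.110 and 19.6% with SE 0.091. In the second scenario it runs from about 6% to 12.5%; in the third, from about 5% to 7%.

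**Teachers.** SE = √(2 × 1.10/(80 × 0.85)) = 0.180. A bias of 0.10 SD would give 8.6%, but since all teachers are approached only differential consent could produce it.

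**The case against.** The strongest reply is that the protocol nowhere says teachers choose the parents. A reader might infer this from the corona-time sentence in section 9.2, but the text names only the channel. The word "some" may mean no more than that few parents will be reached. That stands: the discretion is left open, not described. It also stands that the normal route runs through researchers, so the concern applies there with less force, and that approaching all teachers leaves little room to select them.

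The upper end of the range is also a one-sided worst case: selection in one arm only, and every parent recruited that way. Teachers in both arms may prefer parents they know well, and then little bias remains. Parents recruited by researchers dilute it further. The direction is unknown too: intervention teachers might invite parents they think need help, which would hide an effect.

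There are real safeguards: an independent randomiser, pairs matched on location size within each organisation, a blinded final analyst, and adjustment for the baseline score, age, ethnicity and education. The first two protect the allocation of preschools and the third protects the analysis; none governs who enters afterwards. The adjustment helps but is partial. Parental motivation is not measured, and the adjusted primary model in section 8.1 names only teachers' covariates.

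**Conclusion.** The concealment gap is real and follows from the protocol's text. Allocation comes before inclusion and baseline, and nothing keeps it from those who recruit and respond. The risk is greatest for corona-time parents and smaller for researcher-recruited parents and for teachers.

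The size and direction cannot be derived from the documents. On the assumed values above, the residual bias after baseline adjustment runs from near zero, when both arms select alike, to about 0.2 SD, when only intervention teachers select; the parent sample is sized for 0.35 SD. A residual bias of 0.10 SD would put the parent test's error rate at about 12–20%.

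Two stronger readings are not supported. One is that a spurious effect will arise, or will favour the intervention: the documents show an opening, not a bias. The other is that this point extends to the staff and students who take body measurements. Their blinding is a separate matter that concerns secondary outcomes.

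**What to change.** In section 6.2, state that the independent researcher releases a matched pair's allocation only after both preschools have completed consent and baseline questionnaires, and that training follows the release. This fits the Summary, which counts the 6 months from the start of the intervention.

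In section 9.2, state that in corona times teachers hand the invitation to every eligible parent, and that each preschool records how many were invited and how many consented. A count is enough, so researchers need no list of parents who have not consented.

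The cost is that training waits until both preschools of a pair finish baseline, so a slow preschool delays its partner, plus one simple count per preschool. The sample size does not change.
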